## Abstract

**Background:**

Nearly half of all mental health disorders develop prior to the age of 15. Early assessments, diagnosis, and treatment are critical to shortening single episodes of care, reducing possible comorbidity and long-term disability. In Norway, approximately 20% of all children and adolescents are experiencing mental health problems. To address this, health officials in Norway have called for the integration of innovative approaches. A clinical decision support system (CDSS) is an innovative, computer-based program that provides health professionals with clinical decision support as they care for patients. CDSS use standardized clinical guidelines and big data to provide guidance and recommendations to clinicians in real-time. IDDEAS (Individualised Digital DEcision Assist System) is a CDSS for diagnosis and treatment of child and adolescent mental health disorders. The aim of IDDEAS is to enhance quality, competency, and efficiency in child and adolescent mental health services (CAMHS).

**Methods/design:**

IDDEAS is a mixed-methods innovation and research project, which consists of four stages: 1) Assessment of Needs and Preparation of IDDEAS; 2) The Development of IDDEAS CDSS Model; 3) The Evaluation of the IDDEAS CDSS; and, 4) Implementation & Dissemination. Both qualitative and quantitative methods will be used for the evaluation of IDDEAS CDSS model. Child and adolescent psychologists and psychiatrists (*n* = 30) will evaluate the IDDEAS` usability, acceptability and relevance for diagnosis and treatment of attention-deficit/hyperactivity disorder.

**Discussion:**

The IDDEAS CDSS model is the first guidelines and data-driven CDSS to improve efficiency of diagnosis and treatment of child and adolescent mental health disorders in Norway. Ultimately, IDDEAS will help to improve patient health outcomes and prevent long-term adverse outcomes by providing each patient with evidence-based, customized clinical care.

**Trial registration:**

ISRCTN, ISRCTN12094788. Ongoing study, registered prospectively 8 April 2020 10.1186/ISRCTN12094788

## Background

Mental health disorders today account for more years lived with disability (YLDs) than any other health condition, with close to 30% of all people worldwide having a mental health disorder at one point during their lifetimes [1, 2]. Children and adolescents are particularly vulnerable. Nearly 20% of all children and adolescents at any point in time have a diagnosable mental health disorder [3, 4]. Despite this, no more than one-third of all children and adolescents with mental health disorders worldwide receive the care they require [5].

In Norway, approximately 20% of all children and adolescents are experiencing mental health problems at any point in time [6, 7]. Both, academic pressure at school and social pressure among peers, contribute to children and adolescents reporting more stress now than ever before [8]. While primary care providers (PCPs) often serve as the first point of contact for patients and their families, still most PCPs do not hold adequate training to address complex neuropsychiatric disorders, such as autism spectrum disorder (ASD) and attention-deficit/hyperactivity disorder (ADHD) [9–12].

Inability to receive a timely diagnosis and appropriate early intervention for neuropsychiatric disorders in childhood and adolescence leads to higher risk of suffering from comorbid mental health problems, including alcohol and substance abuse, behavioral problems [9, 13]. Insufficient access to required child and adolescent mental health services (CAMHS), not only directly impacts the health of the patients and their families, but also can be costly for the society as a whole [14–16]. Misdiagnosed or untreated mental health problems in childhood and adolescence can develop into lifelong mental health disorders requiring long-term care services. Across the European Union, the annual accumulated cost of providing mental health care for children and adolescents is estimated to be nearly €21 billion [16]. Undiagnosed or untreated disorders are also detrimental to the society’s future job market and economic stability, with more frequent work absences and lower productivity among individuals struggling with long-term mental illness [17].

Every year, roughly 5% of the child and adolescent population in Norway require specialist care from CAMHS [18, 19]. Among Norwegian twelve-year-olds alone, an estimated 3.4% have ADHD at any point in time; it is one of the most common reasons for referral to CAMHS [18]. If left untreated, ADHD can predispose children and adolescents to psychiatric and social pathology later in life [20, 21]. While Norway ensures every citizen to timely care by law [22], it is essential to optimize the quality of diagnostics and early intervention care for all children and adolescents displaying signs of mental illness. One modern approach to CAMHS quality assurance, that has the potential to be cost efficient and sustainable for long-term needs, is the incorporation of information and communication technologies (ICT), including clinical decision support systems (CDSSs) [23, 24].

A CDSS is a computerized system that offers guidance to clinicians in real-time while they provide clinical care by using existing, evidence based resources [25–27]. A CDSS uses compiled evidence-based resources to provide clinicians with clinically relevant guidance and recommendations to help best meet the needs of each individual patient. CDSSs are not designed to replace clinicians. The architecture of a CDSS typically has three distinct components– a Clinical Knowledge Base (domain of expertise based on clinical guidelines and/or health datasets), a Reasoning Engine (cloud based organization of evidence relative to the patient’s electronic health record (EHR)), and a User-Interface (electronic display that provides alerts and recommendations in response to clinician’s queries) [13, 27]. CDSS model designs however can differ; utilizing standardized clinical guidelines (i.e., DSM-V or ICD-11), and/or aggregated health datasets [27]. A CDSS that uses guidelines translates the guidelines into web ontology language (OWL) modeled computerized-guidelines as the base for clinical guidance. CDSSs that incorporate health datasets, also known as “data-driven” CDSSs, use algorithms and data analytics to identify patterns of care trajectories that are relevant to the patient being seen [28–30]. While both approaches have relative strengths, a CDSS model that is both guideline based and data-driven also allows the clinician to receive evidence-based support that is customized to each individual patient, based on extensive evidence and previous patient cases [27–30].

While CDSS implementation in general medicine has been found to be advantageous for the quality of services [30, 31], there is limited evidence on the use of CDSSs for CAMHS [32]. One reason for such limited research is the lack of accessibility to psychiatric data, especially those pertaining to children and adolescents. From the established studies on CDSSs in CAMHS however, most have identified various limitations, including a lack of integration with the EHR, limited predictive models for diagnosis, and inadequate inclusion of multiple disorders [32]. Norway is in a unique position to develop and implement a CDSS for CAMHS because it can potentially avoid previously identified limitations. Over the past decade, the Norwegian National Association of Child and Adolescent Mental Health (N-BUP), has collected extensive data on CAMHS and compiled unique and rich datasets, based on advanced, multidisciplinary EHRs. However, these datasets have yet to be optimally utilized for subsequent care, as maintaining access requires ethical clearance and completion of a local data protection impact assessment (DPIA) and risk assessment to ensure privacy and confidentiality will not be breached.

This paper presents the study design and protocol for the evaluation of the first CDSS for CAMHS in Norway, the Individualized Digital Decision Assist System (IDDEAS). IDDEAS is an innovative research project, contributing to the HELSEVEL Programme (Programme on Health, Care and Welfare Services Research) and funded by the Norwegian Research Council (NFR). The overall aim of IDDEAS is to improve patient care by providing practitioners with real-time, data-driven and evidence-based guidance that ensures earlier and more precise decision-making, avoids misdiagnosis and reduces inefficiency in patient care practices. The principal benefit of the study is to examine the provision of decision support for clinicians in real-time during clinical sessions and improvement of clinical care.

The objectives of the IDDEAS project include:
Evaluate the clinical utility of IDDEAS for diagnosis and treatment of child and adolescent mental health disordersMeasure clinicians’ perceived clinical usability and appropriateness of IDDEAS for child and adolescent mental health careMeasure the clinical relevance and validity of IDDEAS’ user-interface content for clinical careImplement IDDEAS in local Norwegian CAMHS and establish recommendations for future CDSS design and implementation for child and adolescent mental health disorders

## Methods

### Study design and process

The IDDEAS project is an experimental, mixed-methods evaluation study, within CAMHS in Norway. The study evaluates the IDDEAS CDSS model (see Fig. 1) for diagnosis and treatment in CAMHS in Norway; IDDEAS will use ADHD as the first clinical model paradigm. The study consists of the following four stages:

**Fig. 1 Fig1:**
[figure not shown]
The IDDEAS Clinical Decision Support System Model

*Stage 1: The Assessment of Needs & Preparation of IDDEAS.*

*Stage 2: The Development of the IDDEAS CDSS Model.*

*Stage 3: The Evaluation of the IDDEAS CDSS.*

*Stage 4: Implementation & Dissemination.*

### Stage 1: assessment of needs and preparation of IDDEAS

The preparation of IDDEAS includes the establishment of the IDDEAS Consortium, completion of a stakeholder analysis, clinical guidelines and clinical case vignettes validation, and the user-interface design and modeling. The IDDEAS Consortium consists of local CAMHS clinicians, international CAMHS experts, CDSS and software experts, as well as representatives from various service-user organizations (i.e., ADHD Norge, Bikuben, The National Association for Relatives in Mental Health- LPP Tromsø, etc.).

#### IDDEAS stakeholder validation of clinical guidelines and case vignettes

IDDEAS Consortium will first hold a discussion of the current status of CAMHS in Norway and validate the standardized clinical practice guidelines for inclusion within the IDDEAS CDSS, as well as the clinical case vignettes to be used to evaluate the IDDEAS CDSS model. The IDDEAS Consortium will employ clinicians and CAMHS experts as external collaborators for the validation processes. The fictional clinical case vignettes will be created by the IDDEAS Consortium and will be considered valid fictional representations of patient cases with majority consensus (*n* = 10). Both, the guidelines and the clinical case vignettes will be discussed and validated in collaborative focus group discussions held at the Regional Center for Child and Youth Mental Health and Child Welfare (RKBU), Central Norway in Trondheim, Norway. The clinicians in attendance will not participate in the evaluation of IDDEAS to avoid exposure bias and will receive compensation for their time.

#### IDDEAS user-Interface design

As the final part of the IDDEAS preparation, the IDDEAS IT team will collaborate with the Consortium’s clinicians (i.e., local and international CAMHS experts) to design the IDDEAS CDSS user-interface. The IDDEAS IT team will conduct focus groups with the CAMHS experts in order to identify what is most important to address with the design of the user-interface to ensure sufficient usability and acceptability. The IDDEAS CDSS user-interface will be integrated within the patient’s EHR to display prompts and alerts for clinicians in real time.

### Stage 2: development of the IDDEAS CDSS model

Following the validation of the clinical guidelines and clinical case vignettes, and the development of the IDDEAS user-interface design in Part 1, the model of the system will be developed. The previously collected health datasets (i.e., *BUP-data*) to be included in the Clinical Knowledge Base will be aggregated and de-identified. The IDDEAS research team will follow all formal data protection procedures, including the completion of the local DPIA and risk assessment (i.e. ROS Analysis). The datasets will be de-identified using a list of personal identifiers (PID) data placeholders established by the local IDDEAS research team. Prior to integration of the de-identified data within the model, the IDDEAS IT team will internally test the reliability and functionality of the PID placeholders for adequate de-identification of the health datasets.

As the last step in the IDDEAS CDSS development process, prior to the evaluation of the IDDEAS CDSS model, the functionality of the Reasoning Engine will be tested. The IDDEAS Consortium will collaboratively create a list of clinical competence questions (CCQs) based on a previously validated fictional patient case. The CCQs will be input into the user-interface to simulate a clinician querying the system during a clinical session. The utility of the Reasoning Engine will be assessed based on whether the system optimally receives the CCQs, and returns a set of evidence-based, ranked, recommendations for diagnosis and treatment.

### Stage 3: evaluation of the IDDEAS CDSS model

#### Recruitment and eligibility

Study participants are child and adolescent psychiatrists and psychologists (*n* = 30). Participants will represent four child and adolescent mental health clinics (BUP-clinics); the clinics will be chosen at random in collaboration with the N-BUP (Norwegian Association for Child and Adolescent Psychiatry) representative. Purposive sampling will be undertaken to ensure there is a balance among participants, in regards to gender, location in the country, expertise and socioeconomic status. This approach to sampling will limit bias and ensure inclusion of varied perspectives. Recruitment of participants for enrollment in the study will begin no earlier than August 2020. Participants are deemed eligible if they are currently practicing as a child and adolescent psychologist or psychiatrist in Norway.

#### Sample size

The sample size was calculated based on the optimal power value in order to ensure the size of the sample is appropriate for this study. There is the assumption that the effect of decision support is to increase specificity from 0.50 to 0.80 and only moderately change sensitivity. With the assumption that the effect of decision support is to increase specificity from 0.50 to 0.80 and only moderately change sensitivity, the sample size (*n* = 30) can be calculated with an effect size of at least 1.0 and desired power value of .80 (80%); the assumption of the specificity increase, to detect the statistical significance (*p* < 0.05) on a dichotomous variable with 80% power, the number of subjects required is 30.

#### Procedure

The evaluation of the CDSS model initially will entail assessments of how child and adolescent psychologists and psychiatrists perceive the usability, acceptability, validity, and relevance of the CDSS model for use in their clinical practice. The evaluation of the CDSS model will take place in two phases, as follows: Phase 1. Vignette-Based Evaluation and Phase 2. Live Patient Evaluation. Both phases of the CDSS evaluation will occur in randomly selected CAMHS clinics. The incremental evaluation phases will take place within the trial period of August 2020–2023. Using a pre-post design, for both phases of the evaluation, participants will compare the provision of clinical care with use of the CDSS, to the daily clinical practice, as the control. Prior to participation in the evaluation written consent will be obtained from all participants by the project leader. Participants will be informed their participation is voluntary and they can withdraw from the study at any time without penalty.

##### Phase 1: vignette-based evaluation

After completion of informed consent procedures, including assessments of conflicts of interest, clinicians will be asked to complete a brief demographic questionnaire. They will then be provided the educational manual on how to navigate the IDDEAS system. Clinicians will then be asked to critically appraise ten previously validated clinical case vignettes (i.e., fictional patient cases that have been “referred” for assessment of ADHD). Clinicians will first appraise five of the cases without the use of the system and five using the CDSS. The cases will be randomly allocated by the PhD student with the project and verified by the project leader. The allocation sequence will be computer generated.

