##### Quantitative methods

The Likert scale items will be assessed based on inter-rater reliability in accordance with pre-specified and previously validated criteria. The usability, content validity, and user engagement data will be compiled and analyzed with statistical analysis software (SPSS software platform) to determine whether the criteria are met for each measurement (i.e., SUS ≥ 70; UES ≥ 70; CVI > 0.80) [38]. The criteria will be analyzed by computing the average of the rating scores proposed by participants for each Likert item and finding the degree of inter-rater agreement on the IDDEAS system attributes (i.e., prompt/alert provided in system user-interface).

The sensitivity, specificity, and relevance of the IDDEAS system for ADHD diagnosis and treatment will also be assessed based on overall percentage of agreement among participants on appropriate diagnosis, as well as the proposed biopsychosocial treatment plan. A mixed model logistic regression will be used with correct diagnosis as the dependent variable, decision support (yes or no) and patient status (ADHD or non-ADHD) as fixed effects.

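### Random allocation of the ten vignettes is described without balance by ADHD status, mirroring, or a statement that it is drawn per clinician; a stratified, mirrored per-clinician list would be a free improvement

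*Protocol article*

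**What the plan says.** The section on Phase 1 of the protocol article has clinicians "critically appraise ten previously validated clinical case vignettes". It continues: "Clinicians will first appraise five of the cases without the use of the system and five using the CDSS". So a clinician meets each vignette once, in one condition only. On allocation it says "The cases will be randomly allocated by the PhD student with the project and verified by the project leader" and "The allocation sequence will be computer generated". Nothing more is said about the structure of the list, and the number of vignettes that are not ADHD cases is not given.

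Three other places bear on this:
- The Sample size section assumes that "the effect of decision support is to increase specificity from 0.50 to 0.80", with only a moderate change in sensitivity. It arrives at 30 clinicians.
- The Outcomes section makes sensitivity and specificity, with versus without the CDSS, the measure of the primary outcome.
- The quantitative part of Data analysis specifies a mixed logistic model for correct diagnosis with "decision support (yes or no) and patient status (ADHD or non-ADHD) as fixed effects". It names no vignette term and does not list the random effects.

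**The concern.** Specificity is estimated from the non-ADHD vignettes alone, so what matters is how those few cases fall between unaided and aided reading. Two separate things follow.

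1. **Precision.** A plain draw of five from ten will sometimes put most or all of a clinician's non-ADHD vignettes in one condition. That clinician then contributes little or nothing to the within-clinician comparison.
2. **Validity.** Vignettes differ in difficulty. As no clinician sees the same vignette both ways, difficulty cancels only if different clinicians have different splits, or if the model accounts for vignettes. The sentence on allocation names cases as the thing allocated and is silent on the unit of the draw. Under a single split, a difference in difficulty between the two sets of five would be reported as an effect of the CDSS.

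**Working it through.** **The plan's own figure.** A two-group comparison at effect size 1.0, two-sided 5%, 80% power needs 2 × (1.960 + 0.842)² / 1² = 15.7, so 16 per group and 32 in total, close to the stated 30. A one-sided arcsine comparison of 0.50 with 0.80 gives 29.9 per condition. A two-sided one gives 39 per condition by the usual two-proportion formula. None of these uses the number of vignettes per clinician, so the stated 30 does not show what allocation was assumed.

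**Separate draw per clinician: information.** Let K be the number of non-ADHD vignettes (not stated; 2 to 8 shown) and a the number read aided.
- Within-clinician information is proportional to a(K − a)/K.
- Two given vignettes fall in different conditions with probability 2 × 5 × 5 / (10 × 9) = 5/9. There are K(K − 1)/2 pairs, so the expected information is 5(K − 1)/18.
- The most even split gives floor(K/2) × ceil(K/2) / K.

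| K | Expected, plain draw | Most even split | Ratio | All K in one condition |
|---|---|---|---|---|
| 2 | 0.278 | 0.500 | 56% | 112/252 = 44% |
| 3 | 0.556 | 0.667 | 83% | 42/252 = 16.7% |
| 4 | 0.833 | 1.000 | 83% | 12/252 = 4.8% |
| 5 | 1.111 | 1.200 | 93% | 2/252 = 0.8% |
| 6 | 1.389 | 1.500 | 93% | 0 |
| 7 | 1.667 | 1.714 | 97% | 0 |
| 8 | 1.944 | 2.000 | 97% | 0 |

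For K = 5, a 4:1 split or worse occurs for (1 + 25 + 25 + 1)/252 = 20.6% of clinicians, but a 4:1 split still gives a contrast.

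**Separate draw per clinician: power and error.** Simulations used 30 clinicians, a clinician SD of 0.5 logit and vignette SDs of 0, 0.5 and 1.0 (all assumed), with clinician-clustered errors and 2000 runs per setting. Power for 0.50 to 0.80 was:
- K = 3: 83 to 86% with plain draws, 84 to 87% with stratified mirrored draws.
- K = 5: 96 to 98% with either.

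The largest loss for K = 3, 5 or 7 was about 2 points. Type I error with plain separate draws was about 5%. In a random-intercept logistic model, stratified mirrored allocation lowers the standard error of the log odds ratio from 0.58 to 0.55 (K = 3) or from 0.40 to 0.39 (K = 5).

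**One split for all clinicians.** Take K = 5 split 2:3 and specificity 0.50 in both conditions, and ignore clinician variation.
- Sampling variance of the log odds ratio: 4/(30 × 2) + 4/(30 × 3) = 0.111, so the reported SE is about 0.333.
- Extra variance from vignette difficulty with SD s: s² × (1/2 + 1/3) = 0.833 s². A model without a vignette term does not see it.
- At s = 0.4 the true SD is √(0.111 + 0.133) = 0.494. The 1.96 limit is then really 1.96 × 0.333/0.494 = 1.32 SDs, a rejection rate of about 19%.
- At s = 1.0 the true SD is √(0.111 + 0.833) = 0.972 and the limit is 0.67 SDs, about 50%.

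This approximation runs slightly high. Simulation gives:
- 17.5% (s = 0.4) and 37.6% (s = 0.8) with a random-intercept logistic model;
- 21 to 23% (s = 0.5) and 45 to 48% (s = 1.0) with the clustered analysis, across K = 3, 5 and 7.

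Stratifying the single list by ADHD status does not help: for K = 5 the rates stay at 22% and 45%. With a single unstratified list and K = 3 there is also a 16.7% chance of no specificity contrast at all. Mirrored allocation keeps type I error at about 3 to 5%.

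**The case against.** The article is a condensed account, and the structure of an allocation list is often left to the full protocol. Silence about stratification or mirroring does not show that they are absent. A reader might infer that the design is unstratified and confounded; the text does not support that. It reports a computer-generated sequence, which fits repeated draws across clinicians at least as well as one split of ten cases. With separate draws there is no systematic confounding. This part of the objection stands.

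The type I error figures also need a model without a vignette term. The article names only the fixed effects, and a random effect for vignette would carry case-to-case variation into the standard error. This stands too, so the rates are conditional on both the single split and the model.

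Two further arguments carry less weight. Patient status in the model adjusts for an uneven mix of ADHD and non-ADHD cases, but not for differences in difficulty among the non-ADHD cases. The seven Phase 2 videos also contribute to the primary outcome, but they do not repair the Phase 1 comparison.

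Finally, the precision loss is small except at K = 2, and nothing in the article suggests that number.

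**Conclusion.** The point holds as an improvement to the design, not as an error shown in it. What can be said without knowing the list is modest. Under separate plain draws, estimates are not systematically biased, and 3 to 17% of within-clinician information on specificity is lost for 3 to 8 non-ADHD vignettes, worth at most about 2 power points for 3 to 7.

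The serious consequence, a type I error of roughly 18 to 45% (up to 48% with three non-ADHD vignettes), needs all of the following: one split for every clinician, no vignette term in the analysis, and difficulty SDs of 0.4 to 1.0 logit. The first two are neither stated nor excluded, and the SDs are assumptions, as is the clinician SD of 0.5. Because the current wording permits that case and closing it costs almost nothing, the change is worth making.

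**What to change.** Generate the allocation per clinician, in 15 mirrored pairs: the five vignettes that one member of a pair reads unaided, the other reads aided. With 30 clinicians each vignette is then read by 15 in each condition. This step removes any possible confounding with difficulty.

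Within each list, split the ADHD and the non-ADHD vignettes as evenly as possible between conditions. With five of each, one member of a pair has two non-ADHD vignettes aided and three unaided, and the other member the reverse. This step recovers the small loss of information.

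State both in the Phase 1 section, together with the number of non-ADHD vignettes. The cost is a change to the randomisation script and one sentence of the protocol. No extra clinicians, vignettes or reading time are needed.
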